**The safety and efficacy of modified step-up graded Valsalva manoeuver in patients with vasovagal syncope**

**(Version 1.0 August 20, 2012)**

**Department of Cardiology Puai Hospital**

**Abstract**

Therapeutic options for vasovagal syncope (VVS) remain challenging now. Non-pharmacological therapies, especially the physical maneuvers, are viewed as important and promising strategies for reducing the syncope recurrences. We will plan to recruit 60 VVS patients with syncope history and positive head-up tilt table testing (HUTT). They will be randomly divided into conventional treatment group (NVM group, n=30) and conventional treatment plus standard MVM for 30 days group (MVM group, n=30). The rate of positive HUTT after 30 days treatment and incidence of recurrent syncope during 12 months follow-up will be observed between the two groups. Heart rate variability (HRV) indexes among the three groups and between baseline and after 30 days treatment will be analyzed. The safety and efficacy of the modified Valsalva maneuver (MVM) in VVS patients will be observed. We attempt to find out a new way to treat VVS and discovery the pathogenesis of VVS and the potential mechanism of MVM in VVS.

**Background**

Vasovagal syncope (VVS) is a common clinical syndrome resulting from systemic hypotension due to transient global cerebral hypoperfusion. It characterizes by rapid, brief loss of consciousness that cannot maintain a normal upright position and lasts for a few seconds to a few minutes and spontaneous complete recovery. Although not directly responsible for increased mortality, VVS has a tremendous deleterious impact on the daily quality of life of patients in terms of physical symptoms and injury as well as psychological impact from living in fear of the next syncopal episode . Therapeutic options for VVS remain a challenging problem . Following methods are attempted to reduce syncope recurrences in VVS patients: 1) physical techniques to improve orthostatic tolerance; 2) pharmacologic interventions to prevent depletion of intravascular volume; 3) cardiac pacing to avert bradycardia .

Head-up tilt testing (HUTT) is a usual procedure to diagnose VVS. Previous report showed that VM could induce syncope in volunteer subjects [7]. We asked patients with suspected syncope to perform the classic VM for several times at the beginning and during HUTT in an attempt to increase the positive rate of HUTT in these patients. To our surprise, the HUTT result became negative in 4 out of 8 patients with previous positive HUTT results after VM. This finding encouraged us to test if VM has therapeutic effects in VVS patients. We selected two aged (>65 years) hospitalized male patients with recurrent in-hospital syncope and taught them to perform the classical VM 2 times per day for 5 days under supervision of medical staffs. No syncope occurred during the subsequent hospital stay and the two patients were discharged after 1 week. We asked them to perform the VM once daily for 30 days at home. Until now, they have not occurred syncope for about 3 months.

It is considered that sympathetic activity increased with reduction of venous return and decrease of cardiac preload in the syncopal period of VVS patients at first, and reflex activity of vagus nerve led to the decrease of heart rate and / or blood pressure at present. We think that the therapeutic effect of VM in VVS patients may be related to the regulation of autonomic nervous function [8]. HRV is a common index to evaluate autonomic function. We design the study to test if VM can be an eligible therapeutic option for VVS patients and observe the autonomic nervous function change by HRV indexes in VVS patients. To reduce the likelihood of inducing syncope by classical VM, a modified step-up graded VM (MVM) will be proposed to treat VVS patients by increasing expiration strength and breath-hold time gradually.

**Study design**

Prospective randomized controlled study.

**Objective**

1. To observe the safety and efficacy of a modified Valsalva maneuver (MVM) in VVS patients and find out a new way to treat VVS.

2. To discovery the pathogenesis of VVS and the potential mechanism of MVM on VVS.

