3.3.2.2 Accommodation phase

The MV maneuvers will be performed in the morning session consisted 8 VM and in the afternoon session consisted 7 VM. Patients will be asked to perform VM from A1 level to C2 level gradually. Patients who do not reach the C2 level within 10 days will be excluded from the study.

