3.3.2.3 Standardized MVM therapy phase

The MVM patients will be asked to perform 15 MV at C2 level daily about 50-60 minutes for 30 days.

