3.4 Follow-up

Recurrence syncope of VVS patients will be observed during the follow-up of one year after 30 days therapy.

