**Study flowchart and Study plan**

**Study flowchart**

Syncope patient: HUTT, Holter and randomized

Healthy volunteers: Holter

MVM group: Exclude patients who cannot reach C2 within 10 days at accommodation phase. Conventional treatment plus standard MVM for 30 days

NVM group: conventional treatment for 30 days

CON group

HUTT, Holter after 30 days treatment. Incidence of recurrent syncope during 12 months follow-up

Holter after 30 days

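### Safety is part of objective 1, but the stated syncope window opens only after the 30-day therapy, and MVM patients who miss C2 are excluded after randomisation, so the plan as written would not support calling MVM safe

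*Protocol*

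**What the plan says.** Safety is named in the protocol title, in the Abstract ("The safety and efficacy of the modified Valsalva maneuver (MVM) in VVS patients will be observed") and in item 1 of the Objective ("To observe the safety and efficacy of a modified Valsalva maneuver (MVM) in VVS patients"). No safety outcome is attached to it in any of these places.

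The Background gives a reason to look for harm: "Previous report showed that VM could induce syncope in volunteer subjects". It goes on to say that the step-up graded version was chosen to make this less likely than with the classical manoeuvre.

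Exposure comes in three stages. Threshold testing (3.3.2.1) goes through six levels, A1 to C2. Accommodation (3.3.2.2) lasts up to 10 days, with manoeuvres "performed in the morning session consisted 8 VM and in the afternoon session consisted 7 VM". The therapy phase follows (3.3.2.3): "The MVM patients will be asked to perform 15 MV at C2 level daily about 50-60 minutes for 30 days".

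The syncope outcome is placed after all of this. Section 3.4 reads: "Recurrence syncope of VVS patients will be observed during the follow-up of one year after 30 days therapy". The Statistical analysis section compares recurrence over the 12-month follow-up with a log-rank test.

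Section 3.3.2.2 also states: "Patients who do not reach the C2 level within 10 days will be excluded from the study". The Study flowchart puts this step after randomisation ("Syncope patient: HUTT, Holter and randomized") and in the MVM branch only.

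**The concern.** The natural safety question is whether repeated Valsalva manoeuvres provoke fainting, near-fainting or injury in people already prone to syncope, and whether grading the manoeuvre prevents this. That can only be answered while patients perform manoeuvres, and in all patients who started them. The plan's stated window begins when prescribed manoeuvres have ended, and its exclusion rule removes a group that plausibly includes the least tolerant patients.

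If the plan is followed to the letter, a favourable safety statement could reflect when events were counted and who was left, rather than what happened on treatment. The statistical analysis plan cannot repair this later, because it cannot analyse events that were not collected or patients who were no longer followed.

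**Working it through.** **Plan's own figure.** The protocol gives no safety event rate, target or precision, so there is no safety figure to reproduce. The inputs taken from it are 30 patients in the MVM group (Methods, section 2), 8 + 7 = 15 manoeuvres a day for up to 10 days (3.3.2.2), and 15 a day for 30 days (3.3.2.3).

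**Step 1: exposure against the counting window, per MVM patient**

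| Period | Prescribed manoeuvres | Inside the 3.4 syncope window? |
|---|---|---|
| Threshold testing | six levels, number not given | no |
| Accommodation, up to 10 days | up to 15 × 10 = 150 | no |
| Therapy, 30 days | 15 × 30 = 450 | no |
| Follow-up, one year | 0 | yes |

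Up to 10 + 30 = 40 days and 150 + 450 = 600 manoeuvres (threshold testing not counted) fall outside the window. These are maxima: a patient who reaches C2 early has fewer accommodation days, and one who is excluded never enters the therapy phase. The count describes exposure. It is not a measure of risk.

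**Step 2: patients who leave the results.** The number who will miss C2 is unknown. For an assumed range, with exact (Clopper–Pearson) 95% limits:

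- 1 of 30: 3.3% (0.1% to 17.2%)
- 3 of 30: 10.0% (2.1% to 26.5%)
- 6 of 30: 20.0% (7.7% to 38.6%)

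Under the exclusion rule these proportions are not a planned result, and syncope or injury in these patients would not be followed up.

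**Step 3: what complete counting could show.** With zero events among n patients, the two-sided 95% upper limit is 1 − 0.025^(1/n). For n = 30 this is 1 − 0.025^(1/30) = 11.6%. The chance of seeing at least one affected patient is 1 − (1 − p)^30, where p is the true per-patient risk. For assumed values of p:

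- p = 1%: 26%
- p = 5%: 79%
- p = 10%: 96%

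So even with full counting, 30 patients could miss an uncommon harm, though a common one would probably be seen. Under the stated window, these calculations have no on-treatment data to work on.

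**The case against.** The strongest reply is that this treats silence as a rule. Section 3.4 sets the window for recurrent syncope as an efficacy outcome and does not forbid recording earlier events. Safety tables are often left to a statistical analysis plan, which is not at hand. Section 3 of the Methods says that syncope frequency and related injury are recorded in the patients, and that sentence, unlike the one before it, is not limited to baseline. Section 3.3.2.1 judges tolerance level by level on blood pressure and heart rate, and the exclusion rule itself requires patients who miss C2 to be identified.

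Much of this stands, and it rules out several stronger readings that a reader might infer:

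- *That the trial yields no safety information at all.* Tolerability information does arise in the threshold and accommodation steps. It is simply not named as an outcome to be reported.
- *That anyone who cannot complete the therapy is removed.* The only such rule concerns reaching C2 within 10 days. Nothing removes patients who stop later.
- *That the protocol reports MVM to induce syncope.* The hazard cited is for the Valsalva manoeuvre in volunteers, and the graded version is meant to reduce it.
- *That safety ranks above efficacy.* Objective 1 names them together, with no order of importance.
- *That an excess of events would certainly go unreported.* Investigators may note events informally. The protocol does not require it.

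The core remains. The Methods sentence on syncope and injury sits with disease history and current medications, so it reads most naturally as history-taking; at best it is ambiguous. The 30-day tilt test does detect syncope, but syncope provoked by the test after treatment, as a measure of efficacy. The observation window and the exclusion are fixed in the protocol, not left to a later document.

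**Conclusion.** The point holds in this limited form. Safety is an objective, but the only stated window for spontaneous syncope excludes the whole period of prescribed exposure (up to 40 days), and the one-arm exclusion after randomisation takes out patients who may have tolerated the step-up worst. A claim that MVM is safe would not be supported by the plan as written.

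This rests on two readings: that section 3.4 defines when syncope is observed, and that exclusion from the study means no further follow-up or reporting. The exclusion counts and event risks used in the working are assumptions, and the conclusion does not depend on any one of them. The effect of the exclusion on the efficacy comparison is a separate matter. This should be changed before recruitment, since on-treatment events that are not captured cannot be reliably recovered.

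**What to change.** Amend section 3.4 and Statistical analysis as follows:

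- Record syncope, presyncope and syncope-related injury in both arms from randomisation, through accommodation and the 30 days, into the one-year follow-up.
- Compare syncope and injury between arms over all randomised patients.
- Keep MVM patients who do not reach C2 in follow-up. What treatment they then receive is a clinical matter that this point leaves open.
- Report failure to reach C2 and stopping for intolerance, with reasons, as n/N of all randomised MVM patients with exact 95% confidence intervals.
- Limit any safety statement to what those intervals exclude.

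Sections 3.3.2.2 and 3.4 and the flowchart should be made to agree with this. Blood pressure or rhythm recording at every manoeuvre is not being asked for: it would need substantial extra monitoring and has no counterpart in the NVM arm. If on-treatment events will not be collected, safety should come out of the title and objective.

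The cost is a patient diary or one form page, one table, continued follow-up of the patients who miss C2, and a short amendment. The downside is a little more data collection and a less favourable safety statement with wide intervals.

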**Methods**

1. Study population

Inclusion criteria: we will recruit VVS patients aged between 18 to 80 years old with at least three lifetime syncopal spells associated with positive head-up tilt testing.

Exclusion criteria: Patients will be excluded if they have other causes of syncope, cannot give informed consent, have serious diseases or psychopath. Women who are pregnant, ready to pregnant, or breast-feeding a baby will be excluded.

2. Divided groups

VVS patients will be randomly divided into two groups: NVM group and MVM group, each 30 patients. Healthy control group (CON group) is 30 patients.

2.1 NVM group: Conventional therapy included: 1) Patient education for the importance of taking enough dietary salt and fluid in daily life. 2) Avoid medications such as diuretics and vasodilators.

2.2 MVM group: conventional treatment plus standard MVM for 50-60 minutes once a day for 30 days.

2.3 CON group: Age and gender matched healthy volunteers without syncope will be enrolled as healthy controls.

3. Study methods

All patients will give informed consent for participation in the study. Age, gender, body mass index, heart rate, blood pressure and biochemical indexes will be record at baseline in the three groups. Frequency and duration of syncope, syncope-induced trauma as well as disease history and current medications will be record in VVS patients.

3.1 Head-up tilt testing (HUTT)

HUTT will be performed at baseline and after 30 days in all VVS patients.

The patients are placed in the supine position for 10 minutes to obtain baseline ECG and blood pressure recordings. Electrocardiogram and systolic and diastolic blood pressure are continuously monitored and record. Patients are tilted to a 70° angle for 20 minutes. If syncope do not occur after 20 minutes, 300 mg nitroglycerin is administered sublingually, and the test is continued for another 15 minutes. If positive response occurs, HUTT is terminated immediately. HUTT will be deemed to be positive if syncope or presyncope occurs in association with hypotension (systolic pressure ≤80 mm Hg, diastolic pressure ≤50 mm Hg, or mean arterial pressure decrease ≥25%), and/or cardiac arrhythmia including sinus bradycardia ≤40 bpm, repetitive sinoatrial block or sinus pause >3 seconds, or Mobitz II 2nd or 3rd degree atrioventricular block.

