**Statistical analysis**

Continuous variables will be presented as mean ± standard deviation (SD). Continuous data with normal distribution will be assessed by Student’s *t*-test or one-way ANOVA with Post Hoc test (Bonferroni) as indicated, and non-normal distribution data will be tested by two-tailed Mann–Whitney U test or Kruskal-Wallis non-parametric test as indicated for the baseline characteristics of the three groups. The Chi-square test will be used to compare the ratio or percentages of categorical variables of the three groups. The Chi-square test will be used to compare the positive rate of HUTT at baseline and after 30 days treatment between NVM and MVM groups. The incidences of recurrent syncopeduring 12 months follow-up of NVM and MVM groups will be compared by log rank test of Kaplan-Meier curve. HRV indexes among the three groups will be assessed by one-way ANOVA with Post Hoc test (Bonferroni) for normal distribution data, Kruskal-Wallis non-parametric test for non-normal distribution data. HRV indexes between baseline and after 30 days treatment will be assessed by Student’s *t*-test for normal distribution data, two-tailed Mann–Whitney U test for non-normal distribution data. The relationship between HUTT and recurrent syncope, HRV and recurrent syncope during 12 months follow-up in VVS patients will be assessed by univariable and multivariable Cox proportional hazards models after 30 days intervention. Receiver operating characteristic (ROC) curves of HRV values at 30 days after intervention will be used to predict 12 months follow-up recurrent syncope. The cutoff values of HRV will be derived from ROC curve analysis by maximizing the sum of the sensitivity and specificity. All statistical analyses will be performed with SPSS version 19.0. *P*<0.05 is considered statistically significant.

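### Section 3.1 gives the sublingual nitroglycerin dose for the tilt test as 300 mg; the unit is very probably wrong and should be checked against the source file

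*Protocol*

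**What the plan says.** Protocol section 3.1 sets out the tilt test: supine rest, then a 70° tilt for 20 minutes, then a drug-provoked stage for patients who have not fainted. The drug instruction is "If syncope do not occur after 20 minutes, 300 mg nitroglycerin is administered sublingually, and the test is continued for another 15 minutes". No product, tablet or spray strength, or number of units is given, and no other section states a dose of any drug.

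The test is used throughout the trial:

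- **Schedule.** Section 3.1 says "HUTT will be performed at baseline and after 30 days in all VVS patients".
- **Numbers.** The Abstract says "We will plan to recruit 60 VVS patients with syncope history and positive head-up tilt table testing (HUTT"), and Methods, item 2, confirms 30 in each of the two randomised groups.
- **Eligibility.** Methods, item 1, requires "at least three lifetime syncopal spells associated with positive head-up tilt testing".
- **Outcome.** The Statistical analysis section uses a chi-square test to "compare the positive rate of HUTT at baseline and after 30 days treatment between NVM and MVM groups".

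**The concern.** Hundreds of milligrams is not a credible amount of sublingual nitroglycerin, whereas the same number in micrograms would be. That pattern points to a slip in the unit, not to a dose anyone chose.

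The sentence is an operative instruction to the staff who run the test. They have no second figure in the protocol to check it against. The protocol's own account of the patients makes the unit important: the Background attributes their syncope to systemic hypotension, the control regimen in Methods, item 2.1, tells them to avoid vasodilators, and they may be up to 80 years old. Safety is also part of the first stated objective.

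Only participant safety is at stake, and only if the source document really reads mg. No statistical quantity depends on the dose figure.

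**Working it through.** This is unit arithmetic. The protocol states no calculation behind the dose, so there is no figure of its own to reproduce.

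**Inputs**

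- Dose as shown: 300 mg (Protocol, section 3.1).
- Strength of one sublingual unit: 0.3 to 0.6 mg. This is an assumption; the protocol does not give it.
- Randomised patients: 60 (Abstract; Methods, item 2).
- Tests per patient: 2, at baseline and after 30 days (section 3.1).

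**Dose as shown, in units** (stated dose ÷ assumed unit strength)

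| Assumed unit strength | 300 mg ÷ strength |
|---|---|
| 0.3 mg | 1000 |
| 0.4 mg | 750 |
| 0.5 mg | 600 |
| 0.6 mg | 500 |

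**Sensitivity to the assumption.** If units were ten times as strong, the result would be 300 ÷ 3 = 100 down to 300 ÷ 6 = 50 units. The dose stays implausible, so the conclusion does not turn on the exact strength.

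**Dose if micrograms were meant.** 300 micrograms ÷ 1000 = 0.3 mg. Then 0.3 ÷ 0.3 = 1.0 unit and 0.3 ÷ 0.6 = 0.5 unit, at the lower end of the assumed range. The error factor in that case is 300 mg ÷ 0.3 mg = 1000.

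**Number of tests.** 60 × 2 = 120 tests at most in randomised patients. It would be fewer if MVM patients are excluded in the accommodation phase. People screened with a negative tilt test are not in this count.

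**Who receives the drug.** The protocol does not say what share of patients reaches the drug stage, so the number of doses cannot be derived. The logic of section 3.1 does give one fact: a test is stopped at a positive response, and patients without syncope at 20 minutes go on to the drug. Every completed negative test therefore includes a dose.

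**Could it be a reading error?** In the same section ≤, ≥ and ° are intact, and ± is intact in the Statistical analysis section ("Continuous variables will be presented as mean ± standard deviation (SD")). Chinese characters survive under Expected results. So there is no sign of general symbol loss. However, no micro sign appears anywhere in the text as shown, so this particular character cannot be tested.

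**The case against.** The strongest objection is that the error may not be in the plan at all. A Greek mu set in a symbol font can be read by software as the letter m, which turns micrograms into milligrams with nothing visibly missing. Characters encoded in another way can survive beside it, so the intact ≤, ≥, ° and ± say little about this kind of failure. This stands: the text at hand cannot settle the matter, and the correction has to depend on the source file.

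Second, nothing inside the protocol contradicts 300 mg. The judgement that it is impossible rests on a unit strength brought in from outside. That is true, and the strength is labelled as an assumption. But it would have to be wrong by orders of magnitude before 300 mg became plausible.

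Third, the practical risk is limited. So much drug could hardly be placed under the tongue, clinicians would probably notice, and the test is run with continuous ECG and blood pressure monitoring. This also stands. It lowers the likelihood of harm but does not make a wrong written dose acceptable.

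Finally, the test's role in eligibility and as an outcome does not make the dose any more or less wrong. It shows only that the sentence is an instruction to be followed and not background text.

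**Conclusion.** The concern holds as a suspected unit error in the text as shown. The stated dose is 500 to 1000 times an assumed unit strength of 0.3 to 0.6 mg, and exactly 1000 times too high if 300 micrograms was intended. It would apply in up to 120 planned tests in randomised patients, in those who have not fainted by 20 minutes.

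Confidence is medium, because a misread micro sign cannot be excluded. If the source reads mg, the dose should be corrected on safety grounds. If it reads micrograms, the plan is right on this point. In neither case are sample size, power, alpha or the comparison between the MVM and NVM groups affected.

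**What to change.** Open the source file of section 3.1 and read the unit.

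- **If it reads mg:** correct it by a one-line amendment, presumably to 300 micrograms (0.3 mg), after confirming against the label of the product in use. Writing the word micrograms in full would avoid a further misreading.
- **If it already reads micrograms:** no change is needed.

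The cost is one look at the file and, at most, a one-line amendment. No extra patients, visits or procedures are involved.

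### Undefined presyncope can decide a 30-day tilt test, and nothing keeps the arm from the person who classifies it, so borderline tests can be read in the expected direction

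*Protocol*

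**What the plan says.** Protocol section 3.1 sets a rule with two parts. The first is a symptom: "HUTT will be deemed to be positive if syncope or presyncope occurs in association with hypotension". The second is a measured sign. It is either a pressure criterion, "systolic pressure ≤80 mm Hg, diastolic pressure ≤50 mm Hg, or mean arterial pressure decrease ≥25" per cent, or a rhythm criterion, "and/or cardiac arrhythmia including sinus bradycardia ≤40 bpm, repetitive sinoatrial block or sinus pause >3 seconds", or a listed atrioventricular block. Presyncope ranks equally with syncope in the rule and is not defined anywhere in the protocol. The signals are kept: "Electrocardiogram and systolic and diastolic blood pressure are continuously monitored and record". The call also ends the observation: "If positive response occurs, HUTT is terminated immediately".

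The Study design section reads only "Prospective randomized controlled study". No section mentions masking of the patient, the tilt operator or the person who classifies the test. The MVM arm receives "conventional treatment plus standard MVM for 50-60 minutes once a day for 30 days", and the comparison arm has no sham manoeuvre.

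Under Statistical analysis, "The Chi-square test will be used to compare the positive rate of HUTT" between NVM and MVM, planned at 30 patients each. Expected results states in advance that the MVM rate will be the lower one.

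**The concern.** The pressure and rhythm limits are necessary for a positive test but, on the natural reading of the rule, not sufficient. A patient who crosses a limit and does not faint is positive if presyncope is called and negative if it is not. That call depends on a sensation the patient describes and on a judgement by the operator, with no common definition behind either. The patient certainly knows whether he or she has done an hour of manoeuvres a day for a month. Nothing stops the operator from knowing too.

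The 30-day positive rate is one of the plan's two efficacy comparisons, and HUTT status is also to enter the Cox models for recurrence. A lean on borderline calls would bias the comparison towards the result the protocol predicts. It would also raise the chance of a significant difference when there is none. Because the test stops at the call, the trace cannot show what would have followed. Who classifies an outcome, and with what knowledge, is a matter of trial conduct that belongs in the protocol.

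**Working it through.** The protocol states no rates, effect size or power for this comparison, so there is no planned figure to reproduce. The check asks how far a lean on borderline calls can move the false-positive rate.

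**Inputs from the protocol.** 30 per arm; chi-square test; P<0.05, taken as two-sided; expected direction MVM lower.

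**Assumptions, none given in the protocol.**
- π: true 30-day positive rate, equal in both arms (50% first, then 80% and 90%).
- s: share of positives that are presyncope only (20-50%).
- t: share of negatives that cross a limit without symptoms (10-30%).
- λ: share of borderline tests read in the expected direction (10% or 20%).

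**Formulas.** Observed NVM rate = π + (1−π)·t·λ. Observed MVM rate = π − π·s·λ. The chance of a false result favouring MVM is the exact sum of the two binomial(30) probabilities over all pairs of counts in which NVM exceeds MVM and the uncorrected Pearson chi-square gives P<0.05.

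**Results at π = 50%.** With no lean the chance is 2.6%.

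| λ | s, t | NVM rate | MVM rate | Chance favouring MVM |
|---|---|---|---|---|
| 10% | 20%, 10% | 0.50+0.50×0.10×0.10 = 50.5% | 0.50−0.50×0.20×0.10 = 49.0% | 3.4% |
| 10% | 50%, 30% | 0.50+0.50×0.30×0.10 = 51.5% | 0.50−0.50×0.50×0.10 = 47.5% | 5.1% |
| 20% | 20%, 10% | 51.0% | 48.0% | 4.3% |
| 20% | 50%, 30% | 53.0% | 45.0% | 9.3% |

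In patients: 15 positives in MVM contain 15×0.20 = 3 to 15×0.50 = 7.5 presyncope-only tests. The 15 negatives in NVM contain 15×0.10 = 1.5 to 15×0.30 = 4.5 borderline ones. That makes 4.5 to 12 readings open to a lean, of which a 10% lean moves 0.45 to 1.2 and a 20% lean 0.9 to 2.4.

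**Other base rates, same formulas and shares.** All patients enter with a positive test, so higher 30-day rates are possible.
- π = 80% (2.4% with no lean): a 10% lean gives 3.6-6.1% and a 20% lean 5.1-12.8%.
- π = 90% (2.7% with no lean): a 10% lean gives 4.6-8.6% and a 20% lean 7.0-18.9%.

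**If every reading were open to judgement** (s = t = 100%), π = 50% gives 55% vs 45% and 12.1% at a 10% lean, and 60% vs 40% and 34.9% at a 20% lean.

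**How many readings make a difference from none?** Moving four per arm turns 15 vs 15 into 19 vs 11: chi-square = 60×(19×19−11×11)²/30⁴ = 60×240²/810,000 = 4.27, P = 0.039. With the Yates correction P = 0.071, and with Fisher's test P = 0.070. Three per arm (18 vs 12) gives 60×180²/810,000 = 2.40, P = 0.12. Starting from a near miss, one reading is enough: 24 vs 17 gives P = 0.052 and 24 vs 16 gives P = 0.028.

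**The case against.** The strongest defence is that each positive test is tied to a recorded pressure or rhythm sign. A negative test with no qualifying sign cannot become positive through a generous presyncope call, and a frank faint is not a matter of opinion. This stands, and it limits the problem to tests that cross a limit without syncope. It does not remove the problem, because for those tests the symptom call is decisive.

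A reader might infer more than the protocol supports, in four ways:
- **That assessors know the arm.** The protocol is silent on who classifies the test. Knowledge of the arm is certain only for patients.
- **That the 30-day result as a whole turns on presyncope.** Syncope also counts, and the share of presyncope-only positives is not given. The and/or wording before the arrhythmia list is loose and could even be read as counting an arrhythmia without symptoms.
- **That the false-positive chance is 12% or 35%.** Those figures require every test to be open to judgement, which the measured criteria rule out.
- **That a few readings can create the difference from nothing.** At mid-range rates it takes eight, all in one direction, and the result is then significant only without a continuity correction. One or two suffice only when the arms already differ by almost enough.

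A further tempting step is to recompute the result from the stored traces, counting syncope only, and to require that it agree with the main analysis. This does not work. ECG and pressure traces do not record loss of consciousness. Patients whose test stopped at presyncope never had the chance to faint, so counting them as negative misclassifies them. If presyncope is called early in one arm, the check inherits the same bias and could block a true effect.

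**Conclusion.** The point holds as a gap in outcome assessment: an undefined, partly self-reported symptom can decide borderline 30-day tests, with no step that keeps the arm from the person making the call. The direction of any bias is the one the protocol predicts. Its size cannot be fixed from the protocol. At a true rate of 50% and the borderline shares assumed above, a 10% lean takes the false-positive chance favouring MVM from 2.6% to about 3-5%, and a 20% lean takes it to about 4-9%. These figures rise with the base rate: at 90% positive, a 20% lean could reach about 19%. All of them rest on assumed shares and assumed leans, and none shows that a lean will occur. The inflation is modest in most of this range, but masking cannot be restored once tests have been read, so the safeguard is a cheap improvement worth making.

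**What to change.** Add to section 3.1:
- The existing staff who run and classify the 30-day HUTT are not told the arm and do not teach or supervise the manoeuvre. Patients are asked not to reveal it.
- One written definition of presyncope, chosen by the investigators, applies to both arms.
- Each call is recorded as syncope or presyncope, with the qualifying pressure or rhythm sign, before the arm is disclosed.

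Add to Statistical analysis: the counts of syncope positives and presyncope-only positives at 30 days are reported by arm, descriptively. Do not make a claim on HUTT conditional on agreement with a syncope-only analysis.

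The cost is scheduling, a few lines on the test form and one descriptive table. It assumes that someone other than the person teaching the manoeuvre can run the tilt test, which the protocol does not say. Patients' own symptom reports stay unmasked whatever is done, and the report should state this as a limitation.
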